#### Secondary outcome analyses

The same analysis as described above will be also performed using the remaining scales of the EORTC QLQ-C30 and those of EORTC QLQ-MY20. We will investigate HRQOL profiles by a repeated measures linear mixed model, reporting estimated means, standard deviations (SDs) and 95% confidence intervals. We will assess the clinical relevance of HRQOL differences among patient groups according to previously published guidelines [47, 48]. The type of missing data generating mechanism will be investigated [49], and sensitivity analysis will be performed to assess the robustness of final results. In addition, the definitive HRQOL deterioration (DD) [50] will be assessed on each EORTC QLQ-C30 scale, based on the corresponding smallest change in the score defining a clinically relevant deterioration [47, 48]. We will also investigate the relationship between satisfaction with information provision and HRQOL outcomes and between preferences and patient characteristics. Statistical significance for all analyses is set as α = 0.05.

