Therefore, based on this compelling evidence stemming from the scientific literature, we will primarily investigate the prognostic value of baseline PROs for overall survival, beyond the frailty score [6], to possibly devise a patient-centric frailty score for RRMM patients. Although the frailty score was developed in newly diagnosed (elderly) patients enrolled in RCTs, and we are aware of the differences with the population that we will be enrolled in our study, it is possible that the prognostic value of this score might also hold true in a population that, per se, is even more frail than the study in which this score was developed [6]. The identification of PROs with independent prognostic value in RRMM has the potential to provide a strong rationale for a more patient-centric approach in routine practice. For example, it would greatly support the inclusion of a standard PRO assessment at the time of deciding type of salvage therapy. Based on previous findings in MM patients [13, 14] and in patients with other advanced hematologic malignancies [15], self-reported fatigue will be regarded as the primary outcome for prognostic factor analyses in this study. Furthermore, in a second instance, other PROs will also be investigated to determine whether they provide more accurate prognostic information than fatigue.

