#### Cancer generic quality of life (EORTC QLQ-C30)

The EORTC QLQ-C30 is a brief multidimensional HRQOL measure consisting of 30 items and includes five functional scales (physical, role, emotional, social, and cognitive), three symptom (fatigue, nausea and vomiting and pain) and a global health status/HRQOL scale and six single items (dyspnea, insomnia, appetite loss, constipation, diarrhea and financial difficulties). The validity and test-retest reliability of this questionnaire is highly consistent across different language-cultural groups [39].

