#### Disease specific quality of life (EORTC QLQ-MY20)

The EORTC Quality of Life Questionnaire Multiple Myeloma Module 20 (EORTC QLQ-MY20) will be used to assess disease-specific complaints [40]. This questionnaire contains two symptom scales on disease symptoms and side effects of treatment, one functional scale on future perspective, and one single item on body image.

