#### Primary outcome analysis

The primary HRQOL objective is to investigate the prognostic value on overall survival of baseline self-reported EORTC QLQ-C30 fatigue scale ratings, independent from the clinically-based prognostic frailty score [6]. Differences between groups will be assessed using χ2, Fisher’s exact, Wilcoxon Mann-Whitney and Kruskall-Wallis tests. We will investigate the prognostic value of baseline variables by Cox proportional hazards regression analysis, including the baseline fatigue score, the prognostic frailty risk groups and established prognostic factors in MM. An extended Cox model will account also for possible time-varying confounding factors (e.g. type of treatment). We will use the likelihood ratio test to assess the prognostic information possibly provided by fatigue, in addition to the prognostic frailty score, by the likelihood ratio test. The robustness of final findings will be assessed by a bootstrap re-sampling procedure [45, 46]. Conditional to the actual prognostic value of the fatigue scale, we will develop a fatigue-adjusted prognostic frailty score included in this scale.

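### Eighteen further PRO scales are tested for survival at an unadjusted 0.05, and the stated test does not compare any of them with fatigue, which is the plan's own question

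*Protocol article*

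**What the plan says.** In the protocol article, Primary outcome analysis fits a Cox model with baseline fatigue, the frailty risk groups and established prognostic factors. The inferential step is this: "We will use the likelihood ratio test to assess the prognostic information possibly provided by fatigue, in addition to the prognostic frailty score". A bootstrap check of robustness follows.

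Secondary outcome analyses extends this to the other scales: "The same analysis as described above will be also performed using the remaining scales of the EORTC QLQ-C30 and those of EORTC QLQ-MY20". The same section closes with a general rule: "Statistical significance for all analyses is set as α = 0.05".

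The purpose of looking at the other scales is given under Rationale and clinical significance: "other PROs will also be investigated to determine whether they provide more accurate prognostic information than fatigue".

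The scales are listed in the questionnaire sections. The QLQ-C30 has "five functional scales (physical, role, emotional, social, and cognitive), three symptom (fatigue, nausea and vomiting and pain"), plus "a global health status/HRQOL scale and six single items". The QLQ-MY20 has "two symptom scales on disease symptoms and side effects of treatment, one functional scale on future perspective, and one single item on body image".

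**The concern.** Two things do not fit together.

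First, a whole set of secondary survival tests runs at the same nominal level as the primary test. The article neither labels these tests exploratory nor states any control of error across them. The level is fixed expressly for every analysis, so this is a stated rule and not only a detail left to the analysis plan.

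Second, the test does not match the question. A scale can add to the frailty score and still be less informative than fatigue, or merely echo it. The article names no model holding fatigue and another scale together, no measure of discrimination or prediction error, and no other comparison of the competing models.

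The Rationale section says that PROs with independent prognostic value would support standard PRO assessment when salvage therapy is chosen. A chance finding, or a scale that only stands in for fatigue, could therefore be carried into practice recommendations.

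**Working it through.** **Number of tests.** QLQ-C30: 5 functional + 3 symptom + 1 global + 6 single items = 15. Without fatigue this is 14. QLQ-MY20: 2 + 1 + 1 = 4. Total 14 + 4 = 18. This takes the repeated analysis to be one scale at a time.

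**Chance of a false positive.** The plan gives no familywise figure to reproduce. Assume that none of the 18 scales adds information and that each is tested at 0.05.

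- Expected false positives: 18 × 0.05 = 0.9, whatever the correlation.
- At least one, if independent: 1 − 0.95^18 = 0.603.
- At least one, for normal test statistics with a common correlation. The article gives no correlation, so these are assumed values:

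| Assumed correlation | Chance of at least one false positive |
|---|---|
| 0.2 | 55.5% |
| 0.3 | 51% |
| 0.5 | 40% |
| 0.7 | 28% |
| 0.8 | 21.6% |

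**What the test can say about accuracy.** The model with frailty plus fatigue and the model with frailty plus another scale are not nested in each other. Each likelihood ratio test compares one of them with the frailty model. Neither tests the difference between the two. Two checks show what follows from this. Both use inputs from Sample size determination: HR 1.11 per 10 points, SD 29 and 35% events.

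1. *Two equally prognostic scales.* Cox data were simulated for 312 patients with 35% events, 400 data sets per setting. Each scale had the planned fatigue effect, and the correlation between them was assumed to be 0.5 or 0.7. Separate tests over a frailty-only model found one scale significant and the other not in about 16% of data sets at either correlation. Neither scale was in fact more accurate.

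2. *A scale with no information beyond fatigue.* Deaths: 296 × 0.35 = 103.6. Expected test statistic for fatigue: √103.6 × ln(1.11) × 2.9 = 3.08. For a scale that predicts survival only through a correlation r with fatigue, it is about r × 3.08:
   - r = 0.5 gives 1.54, so the scale is significant about 34% of the time.
   - r = 0.7 gives 2.16, so about 58% of the time.

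   The stated test would call such a scale prognostic and could not show that it only echoes fatigue.

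**Cost of strict adjustment.** Bonferroni over 18 (also Holm's first step) uses 0.05/18 = 0.00278, critical value 2.99. For a scale with the fatigue effect and 103.6 deaths, power at 0.05 is Φ(3.08 − 1.96) = 87%. At 0.00278 it is Φ(3.08 − 2.99) = 54%.

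**Note on the 87%.** The article states 90% power with 296 patients. The stated HR of 1.11, two-sided, needs 114.7 deaths, and 114.7/0.35 rounds up to 328 patients. A log hazard ratio of 0.11 per 10 points gives 295.02, rounded up to 296. That is a separate matter, and the conclusion here does not depend on it.

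**The case against.** The other side has a good deal of weight.

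- **Secondary status.** Fatigue is the one scale named in advance, and the other scales come second, in an observational study. Adjustment across secondary prognostic factors is often settled in the full protocol or analysis plan. This stands as a reason against mandatory familywise control, particularly as power for a fatigue-sized effect would fall from about 87% to 54%. It does not remove the need to say how 18 results at 0.05 will be read.
- **One scale at a time is inferred.** It is the natural reading of repeating the fatigue analysis, but the article does not spell it out.
- **The tests say something about relative value.** A reader might infer that they say nothing. That goes too far. If each scale enters as one term over the same base model in the same patients, ranking by likelihood ratio statistic is the same as ranking by AIC. The inclusion criteria require a full baseline PRO evaluation and all frailty data, which favours a common analysis set. What is missing is a test or interval for the difference from fatigue.
- **Ranking by p-value.** A reader might expect this, but the article does not propose it.
- **The prognostic score.** The plan says: "Conditional to the actual prognostic value of the fatigue scale, we will develop a fatigue-adjusted prognostic frailty score". A reader might infer that this score is overstated by selection among 18 scales. It is not, because fatigue was fixed in advance. Whether the bootstrap repeats any selection step depends on procedures not shown, so no error can be claimed there.

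**Conclusion.** The point holds on two counts. The article states no direct comparison with fatigue, although that comparison is its stated aim. It also runs 18 secondary survival tests at 0.05 with no multiplicity control and no exploratory label.

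The 60% figure should not be read as the expected risk. It needs independent tests and no informative scale among the 18. Scales completed by one patient on one day are correlated, and the study's own premise is that some PROs are prognostic. With assumed correlations of 0.8 to 0.2 and still no informative scale, the chance is 21.6% to 55.5%. This is well above 5%, but it does not support saying that a false finding is likely whatever the correlation.

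A reader might also infer that the primary result is compromised. It is not: the fatigue test is a single prespecified test, and its level is untouched.

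**What to change.** Amend Primary outcome analysis and Secondary outcome analyses as follows.

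1. Keep 0.05 for the single fatigue test.
2. Compare each other scale with fatigue in the same patients. One route is a Cox model with the frailty groups, the established factors and both scales, which shows whether the scale carries information beyond fatigue. The other is the difference from the fatigue model in a prediction measure (AIC or C-index) with a bootstrap confidence interval, which addresses which scale is the more accurate. Either or both can be used; name the choice in advance.
3. Label the 18 scale-by-scale tests exploratory and report Benjamini-Hochberg-adjusted p-values beside the unadjusted ones.
4. If a score is ever built on a scale chosen from the 18, repeat that choice inside the bootstrap already planned.

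The cost is a few sentences and a little more analysis on data already being collected. The downside is that fewer secondary scales will be called significant.

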### Safety considerations

#### Adverse events reporting

All adverse events, whether serious or non-serious including as well documentation of pregnancy exposures and/or pregnancies in partners, will be recorded in the CRF from the time a signed and dated ICF is obtained until completion of the subject’s last study-related procedure. Adverse events will be evaluated according to the NIH-defined common toxicity criteria CTCAE version 4.0. This can be viewed on-line at: https://evs.nci.nih.gov/ftp1/CTCAE/CTCAE_4.03/CTCAE_4.03_2010-06-14_QuickReference_5x7.pdf.

#### Serious adverse events reporting

All events that meet the definition of a serious adverse event will be reported within 24 h of them becoming aware, to the sponsor using a Serious Adverse Event (SAE) Report Form or a pregnancy questionnaire form (also in case of abnormal pregnancy outcomes) where appropriate, regardless of whether they are protocol-specific assessments. Follow-up information regarding the outcome of the pregnancy and any postnatal sequelae in the infant will be required.

The cause of death of a subject in a study, whether or not the event is expected or associated with the product under study, is considered a serious adverse event.

The Investigator, in case of death, has to communicate the event also to his/her local Ethic Committee. The Sponsor will forward information about SAEs to the Ethics Committee according to the new Pharmacovigilance legislation. Information about SUSAR will be forwarded by GIMEMA directly into the EudraVigilance database.

### Ethical considerations

This study is conducted in agreement with the Declaration of Helsinki (Tokyo, Venice, Hong Kong, Somerset West and Edinburgh amendments) and it was approved by the University ‘Sapienza’ Ethics Committee. The written informed consent of the patient to participate in the observational study has to be personally signed and dated by the patient prior to participation in the study. Obtainment of informed consent will be noted in the Registration Checklist form by the Investigator. The original signed and dated informed consent shall remain at the Investigator’s site and must be stored in the patient file and a copy has to be given to the patient. The name or even initials of the patient will not be asked nor recorded at the GIMEMA Data Center. This consent must be obtained in accordance with local governmental regulations and must be approved by the IRB/Ethical committee of each participating center.

## Discussion

The majority of studies that have assessed PROs in MM patients, have broadly focused on newly diagnosed patients. Also, most of these studies have been conducted in RCT settings [4], therefore limiting generalizability of study findings to the wider population typically seen in daily clinical practice. Treatment of RRMM patients is highly challenging and outcome prediction is critical to enhance personalized treatment planning. Therefore, this study broadly aims to generate new evidence-based data to facilitate clinical decision-making in this population. Also, based on previous evidence indicating that PROs add independent prognostic information for survival outcomes, we will possibly devise a patient-centric prognostic score to be used in clinical practice. Results of this project will be published in international peer-reviewed journals and abstracts presented at major international conferences including Annual Meetings of the European Hematology Association, and the American Society of Hematology.

### Trial status

Protocol version number and date: version 1 (13/04/2017)Date recruitment began: November 2017Approximate date when recruitment will be completed: November 2018

## Abbreviations

ADL: Katz Activity of Daily Living
CCI: Charlson Comorbidity Index
CPS: Control Preference Scale
CRFs: Case report forms
CTCAE: Common Terminology Criteria for Adverse Events
ECOG: Eastern Cooperative Oncology Group
EORTC QLQ-C30: European Organisation for the Research and Treatment of Cancer Quality of Life Questionnaire-Core 3
GIMEMA: Gruppo Italiano Malattie EMatologiche dell’Adulto.
HDACs: Histone Deacetylases Inhibitors
HRQOL: Health-related quality of life
HSCT: Hematopoietic stem cell transplantation
IADL: Lawton Instrumental Activity of Daily Living
ImiDs: Immunomodulatory drugs
IMWG: International Myeloma Working Group
ISS: International Staging System
MM: Multiple Myeloma
MoAbs: Monoclonal antibodies
OS: Overall survival
Pis: Protease inhibitors
PRO: Patient-reported outcome
RCTs: Randomized controlled trials
RRMM: Relapsed/refractory multiple myeloma
SAE: Serious Adverse Event
